# PROJECT IDENTIFICATION

## Title

Physical activity and diet as determinants of immune function  
A dieta e atividade física e o seu impacto no sistema imunológico

## Main scientific domain

Exercise Immunology  
Secondary domain: Diet and neuro-immuno-endocrine modulation

## Key-words

Exercise, immune function, immune-suppression, diet, obesity, asthma

## Project start and duration

From 1st September 2010 to 1st January 2015

## LIST OF PUBLICATIONS

**I** Cross-cultural translation and validation of a respiratory infection symptoms questionnaire

---

**II** Upper respiratory tract infection susceptibility in athletes – a 3 months follow-up study

---

**III** Effect of physical training on respiratory infections in the elderly

---

**IV** Effect of an high fat versus healthy diet meal on neuro-immune-endocrine response to exercise

---

**V** Effect of physical activity on immunity

---

## SUMMARY

**Background:** Exercise is related to several acute and long-term changes in the immune system[1]. Respiratory infections have also been studied in relation to physical activity, being those with more sedentary behavior and the population that performs high intensity exercise more susceptible[2]. Moreover different characteristics interfere with this relationship, namely physical fitness, age and also diet. Indeed diet modulates immune functions and inflammatory processes [2, 3]. Specific populations namely obese and asthmatic have an intrinsic relation with this changes, but the exercise effect after a meal have never been studied in these particularly susceptible population[4, 5].

**Main Problem:** In a society where exercise is prescribed by physicians to increase physical condition, improve outcomes and reduce cardiovascular risk, the impact of exercise, acute or chronic, in the immune system is unknown. Specific populations can have different responses towards acute and chronic exercise and specific conditions like the type of ingredients ingested, namely fat meals, can be correlated with this responses. The true effect of exercise in the immune system is unknown.

**Research question:** Understand the effect of physical activity and diet as determinants of immune function.

**Aims:** Obtain a valid instrument to evaluate respiratory infections in Portuguese population; to find characteristics related to a illness-prone profile in high competition athletes during a bout of exercise; evaluate the impact of a moderate exercise program in a susceptible population (elderly); Correlate the effect of diet (high fat meal) in acute exercise response in a specific obese and asthma population; ascertain the physical inactivity impact on the immune system.

### **Methods:**

Study design: An observational study with validation methodology will be applied to evaluate respiratory infections; in prospective cohort study of 12 weeks a group of athletes under high competition levels, respiratory infections and potential risk factors accordingly to literature will be evaluated; an prospective case-control with a moderate- exercise program intervention will compare the impact in respiratory infections in elderly under exercise training or not; a randomized, placebo controlled cross-over trial will evaluate the impact of a high fat/high energy meal challenge in an acute exercise challenge; randomized clinical trial will be used to ascertain the impact of physical activity reduction in the immune function

Selection of participants: For questionnaire validation will be selected participants with respiratory infections; athletes will be selected from a high elite pre-competition level team; elderly will be selected from general population, namely from senior universities and nursing homes; asthma and obese participants will be selected from an university population sample

Sample Size: 281 patients will be chosen as target for evaluation in respiratory tract infections validation; 40 patients will be evaluated in total in swimmers illness-prone study trial; 40 participants will be selected to evaluate exercise program in the elderly; 30 participants, with a

equal number of obese, asthma, obese and asthma and a control will be allocated to the meal interventions (60 participants in total) and a target of 60 participants will be randomized to the physical inactivity intervention.

Measurements: Upper respiratory tract infections number, severity and quality of life impact, immune system markers, complete blood cell count, pro-inflammatory and anti-inflammatory mediators, namely cytokines, and metabolomic.

Main Outcomes: Respiratory Infection Risk in Susceptible Population, Immune markers parameter related with acute exercise and physical inactivity interventions (balance between pro-inflammatory and anti-inflammatory cytokines).

**Expected results:** Obtaining a valid method for upper respiratory infections assessment, evaluate the risk factors related with respiratory infections in a athletes population, namely physical fitness, nutrition and stress showing the multifactorial side of immunosuppression in athletes; risk of respiratory infections in a physical activity and inactivity intervention as well as immune mediators impact related with an acute exercise challenge and the interference with diet previously to the exercise. Demonstrate the effect of exercise in immune system in particularly susceptible population.

## RESUMO

**Introdução:** O exercício está relacionado com alterações agudas e a longo prazo no sistema imune. Estudos anteriores relacionaram infeções respiratórias com a prática de exercício, estando as populações com comportamento sedentário e que realizam atividade física intensa mais susceptíveis. Além disso, diferentes características interferem com esta relação, nomeadamente aptidão física, idade e dieta. De facto, a dieta tem uma função moduladora dos processos imunes e inflamatórios. Populações específicas como obesos e asmáticos têm uma relação intrínseca com estas alterações, mas o efeito do exercício após uma refeição nunca foi estudado nestas populações mais susceptíveis.

**Principal problema:** na sociedade moderna, onde o exercício é prescrito para aumentar a condição física e diminuir o risco cardiovascular, o impacto do exercício no sistema imunitário é desconhecido. Populações específicas podem ter diferentes respostas em relação ao exercício agudo e crónico e condições específicas como tipo de ingredientes ingeridos, como refeições hipercalóricas, podem estar relacionadas com estas respostas. O verdadeiro efeito do exercício no sistema imune é desconhecido.

**Pergunta de investigação:** perceber o efeito da actividade física e dieta como determinantes da função imune.

**Objectivos:** Obter um instrumento válido para avaliar infeções respiratórias na população Portuguesa; encontrar características de um perfil predisponente à doença em atletas de alta competição durante o exercício; avaliar o impacto de um programa de exercício moderado numa população susceptível; correlacionar o efeito da dieta (hipercalórica) na resposta aguda ao exercício numa população específica de obesos e asmáticos; avaliar o impacto da inactividade física no sistema imune.

### **Métodos:**

Desenho do estudo: um estudo observacional com metodologia de validação vai ser aplicado para avaliar infeções respiratórias; num estudo de coorte prospectivo de 12 semanas de um grupo de atletas de alta competição irão ser avaliadas infeções respiratórias e potenciais factores de risco de acordo com literatura; um estudo caso controlo prospectivo com intervenção de exercício moderado irá comparar o impacto das infeções respiratórias num grupo de idosos ; um ensaio randomizado, controlado com placebo estilo cross-over irá avaliar o impacto de uma refeição hipercalórica na resposta aguda ao exercício; um ensaio randomizado irá avaliar o impacto da redução da actividade física na função imune.

Participantes: para validação do questionário foram selecionados participantes com infeções respiratórias; atletas foram selecionados a partir de uma equipa de natação de alta-competição; idosos foram selecionados da população geral, nomeadamente universidades seniores e lares; participantes com asma e obesidade foram selecionados a partir de uma população universitária.

**Tamanho amostra:** 281 doentes foram escolhidos para avaliação da validação do questionário de infeções respiratórias; 40 doentes foram avaliados no estudo de nadadores de alta-competição para avaliar a propensão à doença; 40 participantes foram selecionados para avaliar o programa de exercício em idosos; 30 participantes, em grupos iguais de obesos, asmáticos, obesos e asmáticos e controlo serão alocados para a intervenção com refeição (60 participantes no total) e um alvo de 60 participantes serão randomizados para a intervenção da inatividade física.

**Medidas:** número de infeções respiratórias superiores, impacto na qualidade de vida, marcadores sistema imune, hemograma, mediadores pró-inflamatórios e anti-inflamatórios (citocinas, metaboloma).

**Principais resultados:** Risco de infeção respiratória em populações susceptíveis, parâmetros de marcadores imunes relacionados com exercício agudo e inatividade física (balanço entre citocinas pro-inflamatórias e anti-inflamatórias)

**Resultados esperados:** Obter um método válido para avaliar infeções respiratórias, avaliar os fatores de risco relacionados com infeções respiratórias em atletas (aptidão física, nutrição e stress) de forma a evidenciar o aspeto multifatorial da imunossupressão em atletas; risco de infeções respiratórias na atividade e inatividade física bem como o impacto nos mediadores imunes relacionado com uma prova de exercício agudo e interferência com dieta prévia ao mesmo. Demonstrar o efeito do exercício no sistema imune particularmente em populações susceptíveis.

# 1. RATIONALE

Physical activity is a generic term to any body movement, mediated by skeletal muscles activity and is performed by anyone in order to sustain life [6]. Exercise is frequently used interchangeably with physical activity, but implies an activity performed for a specific purpose such as improvement of physical condition or competition [6]. Acute and chronic exercise induces changes in both number and function of the immune system [1]. Also mucosa immunity, namely that mediated by specific IgA in saliva is depressed in periods of long and intensified training, which could be related to an increase susceptibility to infections[1]. The main focus of exercise and immune impact has been studied in the susceptibility to upper respiratory tract infections (URTI)[2].

Respiratory tract infections are very common and interfere with daily life. Diagnosis is clinical and, until recently, physician confirmation of an infection cause of the symptoms was considered the gold standard. Nowadays this paradigm has been questioned at light of the laboratory identification of pathogens [7]. The use of these techniques are sometimes expensive and time-consuming [1]. Surveys to access respiratory infections have been created, the first of all was the Jackson scale, and more recently the Wisconsin Upper Respiratory Symptoms Survey, which also has an evaluative illness-specific quality of life outcome instrument [8, 9]. These questionnaires have been proven useful to monitor respiratory infections in research conditions[10]. Still, no Portuguese version exists. This type of tool would enable physicians to monitor disease with patients at home and provide a long-term and distant monitoring of this condition and relate it with individual characteristics, physical activity and impact on their lives. Furthermore it would be useful to ascertain the relationship between specific risk factors and immune system susceptibility, namely exercise interventions.

A relationship has been proposed between respiratory tract infections and exercise proposed by a J-shaped model, still not supported by high quality of evidence [1, 2]. This model suggests that moderate exercise may lower the risk for URTI compared to sedentary individuals, but those under high intensity exercise and strenuous exercise periods may raise risk for URTI. It has been proposed a hypotheses that further factors should be considered in this model, namely physical fitness of the individual, concomitant allergy, inflammation, concomitant disease or infection, environmental factors and nutritional status [1, 2, 11]. The sum of these characteristics can define an illness prone profile, specific for each population.

Athletes are an especially susceptible population to respiratory infections, which have an important impact in their performance in high competition challenge. An “open window theory” of altered immunity has been used to explain this susceptibility[12]. After each bout of prolonged exercise it was demonstrated a period of 3 to 72 hours of altered immunity[13]. The acute exercise induces immune system responses, similar to those that occur in the infection period, increased neutrophils, monocytes, natural killer, and a higher concentration of stress hormones, namely catecholamines, growth hormones and cortisol [4, 14]. Furthermore it enhances release of anti-inflammatory and pro-inflammatory mediators [15]. These changes

support the theory of increased susceptibility[4]. Nonetheless the true measure of immune function and its association with immune-suppression is still an unmet need, as cited in the Walsh et al position paper [1]. The main issue is to understand if an athlete is an immune-compromised host and what is the true role of intense and prolonged exercise training in their susceptibility as well as other risk factors that might be involved, namely stress and nutrition[2, 3, 16, 17]. Athletes have reported less episodes of respiratory infections when under normal training comparing with their sedentary peers[3]. In a recent large study, in physically fit and active adults not in high intense training programs showed a reduction of the number and severity of respiratory infections[18].

Exercise and immune system changes are probably in relation with the subject susceptibility. Elderly are frequently recommended to perform physical activity and exercise due to its multiple positive effects on health-related problems[19] and it has been seen as a countermeasure to immune-senescence[20, 21]. It has been shown that the less physically active elderly have an increase on respiratory tract infections[22]. Most of the previous literature focuses on immune mediators response to exercise intervention in elderly, contradictory effects have been seen between cross-sectional and longitudinal studies as it was reported by a recent thorough literature review [21, 23]. This suggests that perhaps other markers should be evaluated, namely specifically patient related outcomes. Only one study performed in postmenopausal women evaluated disease as a main outcome after a 12 months moderate exercise intervention and reported a reduced incidence of common colds[24]. Further investigation is needed to evaluate the true impact of chronic regular exercise in restoring immune function and which factors can be effectively associated to potentiate it. Also, acute exercise might also have a deleterious effect and could limit the beginning of a regular physical activity in illness-prone subjects. This potential effect can be supported by the previously open window theory and immune changes related to them [13]. Acute exercise effect has seldom been studied in populations other than athletes or healthy physical active populations [12, 25, 26]. In Mills et al[27] study proposed that being physically fit is protective of inflammatory responses so the previously seen results might be more significant in sedentary and in persons with chronic inflammatory systemic diseases. Possibly, reducing the physical activity will be associated also with a decreased immune function response. This was previously demonstrated by recent studies of Pedersen group, where there was seen after a short reduction of physical activity a decrease in insulin sensitivity and cardiovascular fitness. Effect of this intervention on immune function has never been studied[28-30].

Populations like asthma patients, obese and asthma-obese also benefit from physical training and it is nowadays widely recommended [5]. Both populations are associated with a chronic inflammatory profile and an increase susceptibility to infections, namely respiratory tract infections[31, 32]. Especially in asthma it is questioned that this seen susceptibility is only an epiphenomenon, infections appear more severe in patients with underlying respiratory disease, or instead a reflection of altered host susceptibility[32]. No previous study has been performed in evaluating acute exercise challenge in this specific population, as epidemiologically the

patient related outcomes are more difficult to relate, there is a need to understand how inflammatory, endocrine and immune function markers behave with acute exercise. Nowadays new forms of inflammation and metabolic assessment appeared which are more informative, namely metabolomic and microbiome, these new mediators can open the knowledge of the exercise impact in this populations[33-35]. This project aims to further study the impact of acute exercise, using immune and new inflammatory biomarkers in these susceptible populations. As previously stated other aspects can be involved in the respiratory infection susceptibility, namely diet.

Dietary interventions have been mainly studied in athletes, namely to be used as an intervention to decrease exercise-induced immune-depression and also to improve performance[4]. High fat meal challenge has been recently studied in a obese asthmatic population and it showed an increase of airway inflammation, mediated by neutrophils and even a decrease in bronchodilator response[36]. In these susceptible populations it will be interesting to evaluate the effects of a high fat diet on post-exercise immunity. Through these results a specific recommendation can be posed to susceptible populations to start exercise activity and do exercise more safely and decrease respiratory infection susceptibility if a healthier diet is chosen. This project aims widen exercise immunology understanding skipping to an individual context susceptibility in order to understand expected results and make the future recommendations on how to prescribe exercise more safely.

## 2.BACKGROUND

Research has been intensified in athlete population to understand their respiratory infection susceptibility. In a systematic review by [name] et al[2], it is agreed that moderate activity may enhance immune function, but high-intensity exercise temporarily impairs the immune competence. Still areas of controversy are suggested by this systematic review; relationship between exercise and upper respiratory infections is affected by poorly known individual determinants such as genetic, fitness, nutritional status and atopy. Mills et al compared physical fit and less fit individuals and showed that in acute response to exercise fit individuals had an attenuation of leukocyte-endothelial adhesion in response to exercise, suggesting a protected inflammatory response to exercise. Reduced physical activity intervention, has recently been used by Pedersen team to evaluate metabolic responses, and showed that this intervention reduced peripheral insulin sensitivity and body composition, furthermore it also showed that this short intervention reduced cardiovascular fitness evaluated by VO2 max [13, 28-30].

Relationship between physical fitness, diet, exercise and immune suppression has been mainly studied in athlete or highly physically active population as reported in the recent published systematic review of Gunzer et al[4]. No conclusion has been withdrawn due to limited research evidence on how to reduce post-exercise upper respiratory symptoms with single macronutrients, namely in high fat nutrition meals [4]. In asthma patients a recent randomizes study by Wood et al, non-obese subjects with asthma were compared with obese subjects who were submitted to a high fat meal challenge versus a low fat meal. It was shown that the participants allocated to the high fat meal showed 4h post-meal an increase in sputum neutrophil percentage, toll-like receptor 4 and a lower relationship of FEV1/FVC, thereby relating the fat consumed to an increase inflammation status. In another study by Meksawan, sedentary men (n=5) and women(n=6) had dietary fat intake during 3 weeks (19% calories and 50% calories) followed by an acute maximal exercise effort test. Evaluated inflammatory mediators of the immune system associated the bout of exercise to an increase of pro-inflammatory mediators which was aggravated by the fat meal for the previous 3 weeks in comparison with normal fat or high fat diet in this study the increase in pro-inflammatory mediators were not seen with a 50% caloric balance.

### **3. RESEARCH QUESTION AND AIMS**

The research question of this project is: how physical activity and diet interfere with the immune system functions, namely respiratory infection susceptibility and illness prone profile.

The main outcomes are:

- Evaluate the use of a respiratory infections questionnaire to diagnose and characterize respiratory infections and their impact on lives in Portuguese patients with respiratory infections over 16 years old. Perform a cross-cultural translation and validation of WURSS-21;
- Evaluate the upper respiratory tract infections risk factors (demographics, fitness profile, inflammatory, metabolomic, neuro-endocrine and environment) in a population with a high level of exercise intensity;
- Test the effect of a controlled, moderate intensity long-term training program in an elderly population;
- Evaluate the effect of a high fat meal compared to a healthy diet meal on the neuro-immune-endocrine response to exercise;
- Study the effect of physical activity reduction on neuro-immune-endocrine mediators and respiratory infections.

## 4.METHODS

### 4.1. Participants and Study Design

#### 4.1.1. Cross-cultural translation and validation of a respiratory infection symptom questionnaire (I)

This is a trans-sectional case control validation research project of a respiratory symptoms questionnaire to be applied in a three months follow-up period during the seasonal peak of upper respiratory infection from January to March 2012 in patients over 16 years old with and without respiratory infections.

#### Participants

All patients that require an unscheduled appointment due to acute illness in a primary health care center (USF Progresso, Perafita, Unidade Local de Saúde de Matosinhos) and from the Department of Allergy and Clinical Immunology from Centro Hospitalar de São João will be recruited. The inclusion criteria for respiratory infections cases are: over or equal 16 years of age, physician diagnosis of respiratory tract infections, with onset of symptoms within 48h and with Jackson score for respiratory infections over 3 or higher. In Jackson score eight symptoms (sneezing, nasal discharge, nasal obstruction, sore throat, cough, headache, malaise and chilliness) are classified as 0=absent, 1=mild, 2=moderate or 3=severe and presence of at least one of the first four cold specific symptoms is required for diagnosis. All those patients that attend to the primary care center or allergy department for other reason except respiratory symptoms/infections will be proposed to enroll the study project as controls. Exclusion criteria are: under 16 years of age, all patients with basal or throat symptoms that started more than 48h before they searched medical care. Results provided from patients with allergy and those without allergy complains will be compared for changes in respiratory symptoms score and in quality of life changes.

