#### 4.3.1. Cross-cultural translation and Validation of WURSS (I)

For statistical analysis of questionnaire validation factorial analysis will be used for content validity evaluation using the 7 identified domains of WURSS-21 plus headache, body-ache and fever, which are included in WURSS-24. This approach combines exploratory and confirmatory procedures, using weighted least square estimates employing diagonal weight matrix techniques to seek common factors between the domains; all questioned items will be included in the analysis. Convergent validity will be provided by Pearson correlations between WURSS-21 scores in the first day and SF-36 scores in the third, as this measures health state in the last 4 weeks. For criterion validity sensitivity, specificity and predictive positive values will be calculated, as well as area under the curve. For internal consistency Cronbach's alpha coefficient in each domain based on the average of scores from the first three days will be calculated and also comparison between the first and last day. To evaluate each day, responsiveness index will be calculated which is equal to minimal important differences (MID)/ $\sqrt{(2\text{mean squared error})}$ .

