##### Sample size calculation

Sample size was calculated assuming the worst proportion for an item, based in the previous published literature, which was chest congestion, that occurred in a prevalence of 75,7%, then assuming a confidence interval of 0,95% and a  $\alpha=0,05$  (with a standard normal deviate for a two-sided  $\alpha$ ), the required number would be 280 participants. This sample is adequate for the target factorial analysis in which 24 items will be used (WURSS-21 + headache, body ache and fever). For controls comparison and predictive validity evaluation, assuming that WURSS has a Sensitivity of 0,85 and Specificity of 0,44, and the fact that 70% of the population experiences a cold in a given year[9, 39], for a desired precision of 0,05 for the sensitivity and for a specificity of 0,1 the sample size population needed will be 281 participants. The largest population of 281 patients will be chosen as target for evaluation.

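### Study I enrols nobody who presents with respiratory symptoms but has no infection, so specificity and AUC for WURSS will overstate its diagnostic accuracy

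*Protocol*

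**What the plan says.** Section 3 sets the aim for Study I: "Evaluate the use of a respiratory infections questionnaire to diagnose and characterize respiratory infections". Section 4.1.1 gives the design: "This is a trans-sectional case control validation research project of a respiratory symptoms questionnaire".

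Under Participants in 4.1.1, cases need a physician diagnosis of respiratory tract infection, "with onset of symptoms within 48h and with Jackson score for respiratory infections over 3 or higher"; in addition, "presence of at least one of the first four cold specific symptoms is required for diagnosis". Controls are patients who attend either site "for other reason except respiratory symptoms/infections will be proposed to enroll the study project as controls". The exclusion criteria, not limited to cases, remove "all patients with basal or throat symptoms that started more than 48h before they searched medical care" (the word printed as basal is read here as nasal).

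Under Validation in 4.1.1, criterion validity compares patients with and without infection, with physician diagnosis as the gold standard, and the Jackson entry rule is cited in support. Section 4.3.1 states the analysis: "For criterion validity sensitivity, specificity and predictive positive values will be calculated, as well as area under the curve".

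**The concern.** The reference standard is physician diagnosis, but entry to the study also depends on the symptoms that WURSS scores. The hardest diagnostic contrast, infection against another cause of the same complaints, is absent by rule. The results would show that WURSS separates people who came with a cold from people who came about something else. They would not show that it identifies infection among people with respiratory complaints, and that is what a claim to diagnose requires. No later analysis can repair this, because the informative patients are never enrolled. Nothing in the protocol limits the accuracy claim accordingly.

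**Working it through.** **Plan's own figure.** Section 4.3.1 gives 281 participants, "assuming that WURSS has a Sensitivity of 0,85 and Specificity of 0,44", with prevalence 0.70 and precision 0.05 for sensitivity and 0.10 for specificity. With n = z²p(1−p)/d²:
- Sensitivity: 1.96² × 0.85 × 0.15 / 0.05² = 195.9 cases; / 0.70 = 279.9, so 280. The stated 281 is reproduced within rounding.
- Specificity: 1.96² × 0.44 × 0.56 / 0.10² = 94.7 non-cases; / 0.30 = 315.5, so 316, which 281 does not reach. That is a separate matter.

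Neither calculation depends on who the controls are, so the present point rests on the eligibility rules.

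**Who enters (4.1.1, Participants).**

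| Attender | Physician's judgement | Enters as |
|---|---|---|
| Onset within 48 h, Jackson 3 or higher with a cold symptom | infection | case |
| Jackson below 3 | infection | neither |
| Presents with respiratory symptoms, e.g. allergic rhinitis | no infection | neither |
| Other complaint, nasal or throat symptoms over 48 h | no infection | neither |
| Other complaint, no symptoms or recent incidental ones | no infection | control |

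Rows three and four would supply false positives, and row two false negatives.

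**Overlap of entry score and test.** Jackson has eight items (4.1.1). Five of them (sneezing, nasal discharge, nasal obstruction, sore throat, cough) are WURSS items (4.2.1), and headache is added to the questionnaire (4.1.1, Procedures). The Jackson range is 0 to 8 × 3 = 24, so the cut-off of 3 is low: three mild symptoms meet it.

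**Direction and possible size for specificity (all inputs assumed).** Let s0 be specificity in controls of the planned kind, s1 specificity in symptomatic non-infected attenders, and w the share of the latter among non-infected people in whom the test would be used. Overall specificity = (1 − w)s0 + w·s1.
- s0 = 0.95, s1 = 0.40, w = 0.20: 0.76 + 0.08 = 0.84.
- s0 = 0.95, s1 = 0.20, w = 0.40: 0.57 + 0.08 = 0.65.
- s0 = 0.90, s1 = 0.20, w = 0.60: 0.36 + 0.12 = 0.48.

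The planned design reports s0 (0.90 to 0.95 here), because w is zero by construction.

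**Both entry rules together (simulation, assumed values).** WURSS and a Jackson-type score are bivariate normal within each group, with separation 0.5 or 1.0 SD, correlation 0.5 to 0.9 and a WURSS threshold midway between the group means. The lowest 10% or 20% of cases and the highest 30% or 50% of non-cases on the Jackson-type score are removed.

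| Separation | Measure | Everyone | After selection |
|---|---|---|---|
| 0.5 SD | sensitivity | 0.60 | 0.64–0.74 |
| 0.5 SD | specificity | 0.60 | 0.70–0.93 |
| 0.5 SD | AUC | 0.64 | 0.73–0.93 |
| 1.0 SD | sensitivity | 0.69 | 0.73–0.84 |
| 1.0 SD | specificity | 0.69 | 0.79–0.98 |
| 1.0 SD | AUC | 0.76 | 0.84–0.98 |

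At a fixed threshold, sensitivity moves only through the case rule (+0.04 to +0.15) and specificity only through the control rule (+0.10 to +0.33). All movements are upward. The simulation cuts non-cases sharply on symptoms, whereas the protocol selects controls by reason for attendance, so these sizes are not estimates for this study.

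**The case against.** The best defence is that diagnosis is a minor use. The protocol calls WURSS an evaluative outcomes instrument and the milestones speak of monitoring. Factor structure, convergent validity, internal consistency and responsiveness do not depend on the choice of controls, and the design is openly labelled case-control. This stands and confines the problem to one component of validity. It does not remove it: Section 3 names diagnosis as an aim and 4.3.1 computes accuracy measures.

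A second defence is that the Jackson rule ties cases to upper-respiratory illness, since a physician diagnosis of respiratory tract infection alone could admit lower-tract cases. That is a good reason not to drop the rule outright.

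Some stronger readings are tempting but not supported:
- A reader might infer that controls are symptom-free. They are defined by why they attend, not by checked absence of symptoms, so recent incidental symptoms are possible.
- A reader might infer that sensitivity is shown to be inflated. With a cut-off of 3 out of 24, few diagnosed infections may be lost among people seeking an unscheduled visit, and no figure is given.
- A reader might take the planning specificity of 0.44 as proof that a symptomatic comparison group was meant. That would need the cited sources, which are not at hand.
- A reader might extend the harm to the swimmers in Study II. There, episodes are defined by self-report, a cold symptom and a Jackson score of at least 2 (4.2.1), not by a WURSS cut-off.
- A reader might think the allergy comparison in 4.1.1 is spoiled. It concerns changes in symptom score and quality of life, which can be compared within cases.

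**Conclusion.** The point holds for specificity and AUC: as measures of diagnostic accuracy they will be biased upward, because symptomatic non-infected attenders are left out by rule. This rests on one reasonable premise, that WURSS scores higher in people who come with respiratory complaints than in people who come for other reasons. Sensitivity may also be biased upward through the Jackson entry rule, but this is a possibility only. The documents do not fix the size of either effect, and the figures in the working are illustrations on assumed values. The bias does not touch the other validity components. It should be corrected, or the claim limited, before accuracy figures are published.

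**What to change.** In 4.1.1, Participants: also admit as controls unscheduled attenders at the same two sites with nasal, throat or cough complaints that the physician judges not to be infection, and apply the 48 h rule to cases only.

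In 4.3.1: report specificity and AUC separately for symptomatic and other controls, and base any statement on diagnostic accuracy on the symptomatic ones. Keep the Jackson rule for the main analysis, but record the score and collect WURSS in all physician-diagnosed infections with onset within 48 h, and report sensitivity with and without the cut-off.

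Whether eligibility can still change is unclear. Section 4.1.1 dates the work January to March 2012, before the protocol date of 10 December 2012. The milestones put the end of translation at month 28 and validation at month 34; counting September 2010 as month 1, these are December 2012 and June 2013. If enrolment is complete, relabel the criterion-validity result in 4.1.1 and 4.3.1 as known-groups validity and remove the claim to diagnose from Section 3.

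Cost: sites and questionnaires stay the same. The accuracy figures will be lower, and some control places go to symptomatic non-infected attenders.
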